## Conceptual framework

The conceptual framework for the Alive & Thrive strategy in Bangladesh is shown in Figure 2. The diagram illustrates all major components of A&T’s strategic mix of interventions in Bangladesh. This framework highlights that behavior change through interpersonal communication between mothers/caregivers and properly trained FLW can create awareness and skills among mothers/caregivers to take proper care of their children. Family support is also considered to be an essential element for ensuring proper IYCF practices. Therefore, other family members, particularly fathers and grandmothers, have been targeted through A&T’s social mobilization and media interventions, to help build support for mothers/caregivers in their homes. Along with behavior change communications, social mobilization, therefore, plays a significant role in building awareness among other household members, such as fathers, in-laws, and adolescents, as well as important people in the community, such as school teachers, religious leaders, and government health professionals. These community members are thought to play an important role in creating a favorable environment for the mothers/caregivers for proper IYCF practices.

Communications via media is another major component of A&T Bangladesh. Behavior change communications using media is intended to help support the interpersonal communication interventions to shape overall behavior change. Finally, the role of advocacy to formulate and/or implement favorable policy to create enabling policy environment for IYCF is crucial and is well-recognized in A&T’s strategy in Bangladesh. A&T’s mandate, in sum, is to improve IYCF practices using multiple platforms through improving mothers/caregiver’s knowledge and skills regarding IYCF practices.

Figure 2. Conceptual framework of Alive & Thrive program in Bangladesh

[figure not shown]

# EVALUATION DESIGN

The impact evaluation of community component A&T interventions delivered through the EHC program uses a cluster-randomized design with repeated cross-sectional surveys at the baseline and endline (Figure 3). For the impact evaluation of A&T’s community-based rural platform, 20 rural subdistricts (*upazilas*) that were part of BRAC’s Essential Health Care (EHC) program platform for A&T were purposively chosen. The objective of this impact evaluation model is to capture the synergistic impact of A&T’s community component along with media communications and private-sector activities, such as the promotion and integration of micronutrient powders.

The impact evaluation is designed to capture impact on all key A&T indicators (stunting, infant and young child feeding (IYCF), and anemia). Using a repeated cross-sectional survey design, impact on stunting will be assessed in children 24-48 months old. The impact on other IYCF practices and anemia will be assessed in children 6-23.9 months old; and the impact on exclusive breastfeeding (EBF) will be assessed in children 0-5.9 months old. A double difference impact analysis as well as analysis by exposure level to interventions will be employed to determine the impact of A&T interventions.

The baseline survey was in April to July 2010, and an endline survey is planned for April to July 2014.

The main outcomes being examined are changes in mean height-for-age Z-score (HAZ) and changes in the prevalence of childhood stunting between baseline and the post-intervention survey. Other core impact indicators for A&T in Bangladesh include changes in age-appropriate WHO-recommended IYCF practices among children under 2 years of age (EBF for children 0-5.9 months old and breastfeeding + age-appropriate complementary feeding for children 6-23.9 months old) and anemia among children 6-23.9 months of age.

In Bangladesh, 100 sub-districts, across five of six divisions, were selected by BRAC as possible A&T intensive areas based on high poverty and stunting levels, and sub-districts that were not included in the government National Nutrition Program. This list was narrowed to 78 based on geographic proximity, size, and other operational aspects to ensure homogeneity across the sample. Within each division, four sub-districts were then randomly selected for inclusion in the evaluation sample using a computer program, for a total of 20 sub-districts. Sub-districts within each division were then randomly assigned, using a computer program, to either the *intensive* (10 sub-districts) or *non-intensive* (10 sub-districts) intervention. The randomization process was carried out in the presence of BRAC and A&T staff and the program evaluators in BRAC’s headquarters in Dhaka.

The baseline survey was conducted in 20 rural *upazilas* that are part of BRAC’s Essential Health Care (EHC) program platform for A&T. The baseline survey had three components—(i) household survey, (ii) community survey, and (iii) staff survey.

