## Detailed statistical analysis approach

The statistical analyses will include intent-to-treat analyses, unadjusted and adjusted, for primary impact indicators. Several other analyses related to establishing plausibility of impacts will also be undertaken.

1. **Impact estimates**

Impact estimates in Bangladesh will be double difference estimates of changes in key impact indicators. This takes into account changes over time between baseline and endline in the intervention and comparison groups, and differences between groups at these times. The impact estimates will yield (1) **percentage point and percentage changes** for IYCF practices and stunting, wasting, and underweight, and anemia (Bangladesh only); and (2) change in **mean Z scores** for height for age, weight for age, weight for height, and hemoglobin (Bangladesh only).

Analyses will be done separately for each critical age group, e.g., exclusive breastfeeding will be assessed only in children 0-5.9 months old, complementary feeding in children 6-23 months old and anthropometry impacts in children 24 months and above. These reflect the different sample age groups for the impact evaluation. All analyses are in Stata.

Analyses will focus on the following:

- ***Pure* *Intent-to-treat*** analyses based on the original evaluation design and original age groups, using child-level data and fixed-effects analysis to achieve double difference estimates. The fixed-effects analysis will account for village, the smallest level repeated between baseline and endline. Further adjustment for geographic clustering at provincial/divisional, district and commune/subdistrict level will be done using random- or fixed-effects to adjust for clustering if needed; the need for this is not likely because of the accounting of variation among villages.
- ***Pure intent to treat in high potential for exposure age groups* –** this analysis will focus on the stunting indicator and capture impact estimates in an age group of children who are mostly likely, because of their age, to have been exposed to A&T’s interventions early in infancy and for the longest duration. This is the 24-35 month age group in both Bangladesh and Vietnam. We will examine the pattern of HAZ across the full 0-59 month age range, and look at impacts on stunting beginning at the age when HAZ begins leveling off i.e. possibly beginning at 18 months of age. We will use fixed-effects regression models to adjust for village clustering as above.

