# Annex 2. Randomization of upazila for Alive & Thrive baseline study in BRAC EHP areas

| **District** | **Name of *upazilas*** | **Randomized to** |
| --- | --- | --- |
| ***Dhaka Division*** | | |
|  | Hossainpur | A&T |
|  | Pakundia | A&T |
|  | Sonargaon | No A&T |
|  | Araihazar | No A&T |
| ***Chittagong Division*** | | |
|  | Sonagaji | No A&T |
|  | Dagonbhuian | No A&T |
|  | Sonaimuri | A&T |
|  | Kompaniganj | A&T |
| ***Rajshahi Division*** | | |
|  | Nandigram | A&T |
|  | Kahalu | A&T |
|  | Parbatipur | No A&T |
|  | Chirirbandor | No A&T |
| ***Khulna-Barisal Division*** | |  |
|  | Damurhuda | A&T |
|  | Alamdanga | A&T |
|  | Bheramara | No A&T |
|  | Daulatpur | No A&T |
| ***Sylhet Division*** | | |
|  | Madhapur | A&T |
|  | Lakhai | A&T |
|  | Jointapur | No A&T |
|  | Goainghat | No A&T |

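### Annex 2 lists same-arm upazilas in adjacent pairs in all five divisions, so the unit actually allocated should be confirmed and the main intervals tied to it

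*Combined protocol and SAP*

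**What the plan says.** Evaluation Design describes two random steps within each of five divisions. First, "four sub-districts were then randomly selected for inclusion in the evaluation sample using a computer program, for a total of 20 sub-districts". Second, "Sub-districts within each division were then randomly assigned, using a computer program", to give ten per arm. Sample Size and Power Calculations takes the upazila as the cluster and counts 20 of them. The title of Annex 2 also names the upazila: "Randomization of upazila for Alive & Thrive baseline study in BRAC EHP areas".

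Annex 2 gives the result in this row order:

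| Division | Row 1 | Row 2 | Row 3 | Row 4 |
|---|---|---|---|---|
| Dhaka | A&T | A&T | No | No |
| Chittagong | No | No | A&T | A&T |
| Rajshahi | A&T | A&T | No | No |
| Khulna-Barisal | A&T | A&T | No | No |
| Sylhet | A&T | A&T | No | No |

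For example, Dhaka opens with "Hossainpur | A&T" and Chittagong with "Sonagaji | No A&T". The first column is headed District, but its cells are blank in the text supplied. That may be a loss in extraction and is not treated here as a fault in the plan.

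On the analysis, the SAP uses village fixed effects and says: "Further adjustment for geographic clustering at provincial/divisional, district and commune/subdistrict level will be done using random- or fixed-effects to adjust for clustering if needed". It then adds that this need is unlikely, because variation among villages is already accounted for.

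**The concern.** Individual 2:2 assignment can give six orders in a division, and only two of them put the same-arm upazilas next to each other. Seeing this in all five divisions raises the question of whether upazilas were allocated singly or two at a time. The table has a District column, so a pair might be two upazilas of one district.

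The answer decides how many independent units the trial has. Village fixed effects remove stable differences between places. They do not remove a change between 2010 and 2014 that is common to an upazila or a pair of upazilas. If pairs were allocated, a change shared within a pair falls wholly on one arm in that division. An interval clustered by upazila would then be too narrow. If upazilas were allocated singly, upazila-level inference is right. Neither case is served by an analysis that stops at the village.

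**Working it through.** **1. The plan's own figure.** Inputs from Sample Size and Power Calculations: stunting 43% v 36.5%, ICC 0.005, alpha 0.05, power 80%, 1,100 per arm, 20 clusters. With 10 clusters per arm, m = 1,100/10 = 110 and the design effect is 1 + 109 × 0.005 = 1.545. The unclustered size is 700 per arm one-sided, and 700 × 1.545 = 1,082, within 2% of 1,100. Two-sided it is 889 × 1.545 = 1,374. So the stated size rests on ten independent upazilas per arm and is reproduced only with a one-sided test.

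**2. The Annex 2 pattern.** Each division has C(4,2) = 6 possible 2:2 allocations, of which 2 give adjacent pairs, so the probability is 1/3. For five divisions it is (1/3)^5 = 1/243 = 0.41%. This assumes that list order was fixed without regard to arm. If rows were grouped by arm after allocation, the probability is 1. Chittagong's reversed order rules out a uniform A&T-first sort. It does not rule out grouping by arm in arbitrary order.

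**3. What changes if pairs were the unit.**

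| | Upazilas allocated singly | Pairs allocated |
|---|---|---|
| Units | 20 | 10 |
| Residual df with division strata | 20 − 5 − 1 = 14 | 10 − 5 − 1 = 4 |
| Possible allocations | 6^5 = 7,776 | 2^5 = 32 |
| Smallest two-sided permutation p | 2/7,776 = 0.00026 | 2/32 = 0.0625 |
| t multiplier (two-sided 5%) | 2.14 | 2.78 (29% larger) |

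**4. Size of the error if pairs were allocated but the upazila is analysed.** Let s be the share of true between-upazila variance common to a pair. The documents give no value, so s = 25-75% is an assumption. Cross-sectional ICCs stand in for the ICC of change, which is a second assumption. Sampling error among children is not shared, so the correlation between the two upazila means in a pair is

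rho = s × m × ICC / [1 + (m − 1) × ICC],

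and the true SE exceeds the one expected under independence by the factor √(1 + rho). Type I error is simulated for a nominal 5% two-sided upazila-level test with division effects (14 df). The cluster sizes are 1,100/10 = 110 and 500/10 = 50. The ICC of 0.005 is the planning value; the others are the baseline values in Table 3.

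| Outcome | ICC | m | rho at s = 25% to 75% | SE inflation | Type I error |
|---|---|---|---|---|---|
| Stunting | 0.005 | 110 | 0.09 to 0.27 | 4-13% | 6-10% |
| Stunting | 0.02 | 110 | 0.17 to 0.52 | 8-23% | 8-15% |
| HAZ | 0.05 | 110 | 0.21 to 0.64 | 10-28% | 9-19% |
| EBF | 0.12 | 50 | 0.22 to 0.65 | 10-29% | 9-19% |

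At s = 0 the inflation is zero and the test holds 5%. A t test on the five within-division pair differences (4 df) holds 5% whatever the value of s.

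**The case against.** The strongest reply is that the documents name the unit three times, in Evaluation Design, in the sample-size section and in the title of Annex 2, and each time it is the sub-district. Annex 2 is a table of results and may simply have been laid out by arm. The pattern was also noticed first and its probability worked out afterwards. Allocation by district would further require each division's random draw of four sub-districts to have produced two districts with two upazilas each, so the selection step would probably be misdescribed as well. All of this stands, and it is why the point is a query and not a finding.

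A reader might infer more: that the trial randomised ten districts, that its standard errors are 12-32% too small, and that its 5% tests reject 9-22% of the time. The documents do not support this. No two upazilas can be seen to share a district. Those larger figures arise only if the 25-75% sharing is applied to the whole variance of an upazila mean, including sampling error among children.

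The plan also has partial safeguards. The community questionnaire records natural disasters and other organisations, the household survey records economic shocks and food security, and the SAP intends to adjust for differential change in underlying determinants. These help with measured changes. They do not settle which unit was allocated or make a village-level interval valid.

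**Conclusion.** The point holds as a query with a conditional consequence. The adjacent pairs are there in all five divisions, and they sit awkwardly with individual assignment: 0.4%, on the condition that list order is unrelated to arm. Whether that condition is met is unknown, and allocation by pair or district is not shown.

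If pairs were allocated, upazila-level intervals would be too narrow by an amount that depends on the outcome: least for stunting at the planning ICC, most for EBF and HAZ. All the non-zero figures rest on the assumed sharing and on cross-sectional ICCs as a proxy for change.

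One part does not depend on the answer. The SAP's expectation that nothing above village level will need adjustment is wrong under either reading, because the allocated unit is at least the upazila.

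**What to change.** Check the randomisation record, reconcile Evaluation Design with Annex 2, and state the districts, the order of the list and the unit assigned. In Detailed Statistical Analysis Approach, replace the remark about adjustment above village level with a rule that the main intervals follow the allocated unit:

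- **Record shows upazilas drawn singly:** keep the upazila as the unit (20 clusters, division strata, 14 df) and say so.
- **Record shows pairs allocated together:** correct Evaluation Design and restate the 20 clusters in the sample-size section as 10 allocated units. Base the main intervals on five within-division pair differences in change (t on 4 df), and report the upazila-level result as secondary.
- **Record silent:** keep the upazila-level analysis as main and give the pair-level analysis as a sensitivity analysis.

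The cost is a look at an existing record and some SAP wording. If pairs were allocated, the intervals widen: the t multiplier alone is 29% larger, and an exact two-sided permutation test could not go below 0.0625. For that reason the pair-level analysis should not become the main one on the row order alone.

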**Figure 3. Impact Evaluation Design**

**
[figure not shown]
**

## Sample size and power calculations

Sample sizes were estimated based on detectable differences between A&T and non-A&T *upazilas* for three separate sets of indicators: 1) exclusive breastfeeding (EBF) rates, 2) complementary feeding practices, and 3) stunting. Our sample size estimates accounted for randomization at the cluster (i.e., *upazila*) level rather than at the individual level. Surveys are repeated cross-sectional, surveying different households/children from the same communities.

The estimated sample sizes for each treatment arm, calculated prior to the baseline survey, was 500 infants 0-5.9 months old for EBF, 500 children 6-23.9 months old for complementary feeding-related practices, and 1,100 children 24-47.9 months old for stunting. Thus, the total proposed sample size was 4,200 children 0-47.9 months old. This sample size was estimated to allow us to detect expected differences in the outcomes outlined below, in a total of 20 clusters with an inter-cluster correlation (ICC) of 0.005, a significance level of 0.05, and power of 80 percent.

A sample size of 500 children aged 0-5.9 months of age was deemed sufficient to detect an increase in EBF rates by approximately 49 percent (from 43 percent to 64 percent); a sample size of 500 children aged 6-23.9 months of age is sufficient to detect an increase in several complementary feeding practices by at least 25 percent; a sample size of 1,100 children aged 24-47.9 months of age is sufficient to detect a reduction in stunting by 15 percent (from 43 percent to 36.5 percent).

Detailed sample size calculations are presented in **Table 3**.

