**Table 3: Sample size calculation for household survey**

|  | **Baseline sample size (same proposed for endline)** | **Baseline (%)** | **Detectable difference with sample size proposed for endline survey**** | **Intra-class correlation at baseline (estimated at upazila level)** | **Minimum sample size for detectable differences** |
| --- | --- | --- | --- | --- | --- |
| Stunting (24-47.9m) |  | 50.9 | 10 pp | 0.02 | 920 (detecting a 9 pp difference will require double this sample size) |
| HAZ (24-47.9m) |  | -2.0±1.2 | 0.35 | 0.05 | 519 |
| EBF (0-5.9m) |  | 49.9 | 20.0 | 0.12 | 390 |
| Minimum acceptable diet (6-23.9m) |  | 14.8 | 10 | 0.04 | 323 |
| Anemia among children  6-23.9 mo |  | 74.7 |  | 0.00 | 284 |

**Based on at least maintaining levels seen in the PE 2013 survey (where data available; data on stunting and anemia not available in PE 2013).*

***Detectable differences are estimated for endline-only comparisons between A&T-intensive and A&T-non intensive; double difference estimates will ensure greater statistical power.*

For the FLW survey at endline, we will again interview BRAC frontline workers delivering services in the 200 villages covered in the sampling for the evaluation. We estimate that the interviews would cover up to 300 SS, 100 SK, and 100 PK.

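### The plan's 80% power for EBF holds at its pre-baseline ICC of 0.005 but is about 69–74% (two-sided, endline-only) at Table 3's ICC of 0.12; from the printed 49.9% baseline, Table 3's 390 fits only an undeclared one-sided test

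*Combined protocol and SAP*

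**What the plan says.** Under Sample size and power calculations: "The estimated sample sizes for each treatment arm, calculated prior to the baseline survey, was 500 infants 0-5.9 months old for EBF". The section adds that a sample size of "500 children aged 0-5.9 months of age was deemed sufficient to detect an increase in EBF rates by approximately 49 percent". The target is an increase "from 43 percent to 64 percent", "in a total of 20 clusters with an inter-cluster correlation (ICC) of 0.005, a significance level of 0.05, and power of 80 percent". Evaluation Design gives the allocation: sub-districts were assigned "to either the *intensive* (10 sub-districts) or *non-intensive* (10 sub-districts) intervention".

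The EBF row of Table 3 reads "49.9 | 20.0 | 0.12 | 390": baseline percentage, detectable difference in points, baseline ICC at upazila level, and minimum sample size. The table's notes say that the differences are for an endline-only contrast between the two arms, and promise that the double difference will have more power. The Detailed statistical analysis approach makes the double difference the impact estimate.

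On the test itself the plan gives only "a significance level of 0.05". It does not say one-sided or two-sided.

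**The concern.** The two places use ICCs that differ 24-fold (0.12 / 0.005). The sufficiency statement for 500 infants stands unqualified beside an ICC that undoes it. Table 3 uses the larger ICC but still shows a modest minimum, which looks too small for a conventional two-sided test with 10 clusters per arm.

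EBF is part of hypothesis 1 and has its own planned manuscript. A reader who accepts 80% power for 20 or 21 points would give a non-significant EBF result more weight than the endline contrast can bear. The figure of 390, in a column of minima, could also be taken as enough for the endline survey, although the table's heading proposes the same sample as at baseline.

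**Working it through.** **Inputs.** From the sample size section: 500 per arm, 43 v 64 percent, alpha 0.05, 80% power, ICC 0.005. From Evaluation Design: 10 upazilas per arm. From Table 3: 49.9%, 20 points, ICC 0.12, minimum 390. Assumptions: 390 is per arm, upazilas are of equal size, and the contrast is unstratified.

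**Formulas.** Design effect DE = 1 + (n/10 − 1) × ICC; effective size = n/DE; SE = √[(p₁q₁ + p₂q₂)/(effective size)]. Normal power = Φ(difference/SE − z), with z = 1.960 two-sided or 1.645 one-sided. I also give a noncentral t on 18 df, since there are only 20 clusters.

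**1. The plan's own figure (500 per arm, ICC 0.005).** DE = 1 + 49 × 0.005 = 1.245; effective size 401.6. p₁q₁ + p₂q₂ = 0.2451 + 0.2304 = 0.4755; SE = 0.0344; 0.21/0.0344 = 6.10. Power exceeds 99.9%. About 90 infants per arm would have been enough, so 500 is ample on this input.

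**2. Same target at ICC 0.12.** DE = 1 + 49 × 0.12 = 6.88; effective size 72.7; SE = 0.0809; ratio 2.596. Two-sided power is Φ(2.596 − 1.960) = 73.8%, or 69.0% by t. Two-sided 80% at 500 per arm holds only up to an ICC of about 0.10 (normal) or 0.087 (t).

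**3. Table 3's 390 (49.9 v 69.9 percent, ICC 0.12).** DE = 1 + 38 × 0.12 = 5.56; effective size 70.1; p₁q₁ + p₂q₂ = 0.2500 + 0.2104 = 0.4604; SE = 0.0810; ratio 2.469.

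| Infants per arm | One-sided normal | One-sided t | Two-sided normal | Two-sided t |
|---|---|---|---|---|
| 390 | 79.5% | 76.7% | 69.5% | 64.6% |
| 500 | 80.7% | 78.0% | 71.0% | 66.2% |
| unlimited | 85.2% | 82.7% | 76.8% | 72.1% |

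If 390 were the total over both arms, power would be lower still: 195 per arm has effective size 195/3.22 = 60.6.

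**4. The ceiling.** With 10 upazilas per arm the effective size cannot exceed 10/0.12 = 83.3. Two-sided 80% needs (1.960 + 0.842)² × 0.4604/0.04 = 90.3. At ICC 0.115, the low end of rounding, the ceiling is still 78.5% (normal). The limit depends on the comparison rate: a 20-point difference becomes attainable in principle once that rate reaches about 59% (pooled variance; about 57% unpooled, 62% by t).

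**5. Detectable difference from 49.9%, two-sided.** At 500 per arm: 22.1 points (normal) to 23.2 (t). At 390: 22.4 to 23.6.

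**6. Do other Table 3 rows suggest a one-sided test?**
- HAZ (SD 1.2, difference 0.35, ICC 0.05): one-sided unclustered n = 2 × 1.44 × 6.183/0.1225 = 145.35. Clustered, this is 10 × 145.35 × 0.95/(10 − 145.35 × 0.05) = 505, near the printed 519. Two-sided it is about 2,270.
- Stunting: the table says that 9 points needs double the sample for 10. One-sided, 1,495/760 = 1.97; two-sided, 10,678/1,657 = 6.4. The printed 920 itself is matched one-sided with a continuity correction (918).
- Minimum acceptable diet (323) fits neither reading for 14.8 to 24.8 percent (817 one-sided, 12,662 two-sided). The pattern is suggestive, not proof.

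**7. Double difference.** Assume 500 per arm per round, ICC 0.12, and a comparison arm that stays at 43 percent while the intensive arm goes from 43 to 64. Let r be the between-round correlation of upazila effects, and v_b and v_e the values of pq at baseline and endline. Each arm contributes variance 0.12 × (v_b + v_e − 2r√(v_b v_e))/10 + 0.88 × (v_b + v_e)/500.

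| r | SE | Two-sided normal power |
|---|---|---|
| 0 | 0.1153 | 45% |
| 0.5 | 0.0866 | 68% |
| 0.6 | 0.0796 | 75% |
| 0.7 | 0.0720 | 83% |
| 0.9 | 0.0535 | 97–98% |

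It equals the endline-only 73.8% at r of about 0.58.

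**The case against.** The strongest reply has four parts.

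- The 500 is labelled as a pre-baseline calculation and is correct at its own ICC, and Table 3 already re-estimates with 0.12. This stands. A reader might infer that the sizing was computed wrongly; step 1 shows that it was not.
- The plan does not declare a two-sided test either, and one-sided 390 reproduces to within half a point of 80%. This also stands. It leaves a choice that must be stated, because a bare 5% level is ordinarily read as two-sided. Even one-sided, 390 reaches only 76.7% when the small number of clusters is allowed for.
- Table 3 prints no endline rates, and its notes refer to levels from a 2013 survey that the documents do not reproduce. For an illustrative 65 v 85 percent, 390 per arm gives 80.3% two-sided (normal; 75.8% by t). A reader might therefore go too far in inferring that 20 points cannot be detected at any sample size. That holds only near the printed 49.9%.
- The impact estimate is the double difference, and randomisation was within divisions. Neither is captured by an unstratified endline contrast. True, but Table 3 sizes that contrast itself, and step 7 shows that its promise of more power is conditional.

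**Conclusion.** The concern holds as a mismatch between stated sensitivity and the trial's own baseline ICC, not as an error in the pre-baseline calculation. At ICC 0.12, power for 43 v 64 percent is 69–74% rather than 80%, so the two-sided endline contrast would miss that effect in about 26–31 of 100 such trials. For 20 points from 49.9%, power is 65–70% at 390 and 66–71% at 500, with a ceiling of 72–77%.

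These figures rest on a two-sided 5% test, 10 equal-sized upazilas per arm, no gain from stratification, and an ICC that is itself estimated from 20 upazilas. A reader might infer that the EBF impact analysis is underpowered. The documents do not support that: double-difference power could be anywhere from about 45% to 97% for correlations from 0 to 0.9, and the plan gives no value. Nor does the plan say that a null result would be read as excluding 20 points, or propose cutting the endline sample to 390.

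**What to change.** - **Sample size section.** Keep the 500 as the historical calculation. Add that at the baseline ICC of 0.12 it gives about 70% two-sided, endline-only power for 43 v 64 percent.
- **Table 3, EBF row.** State the sidedness and the assumed endline rates in both arms. Give the two-sided detectable difference of about 22–23 points at 500 per arm from a 49.9% comparison rate. Drop 390 as a sufficient minimum, or label it one-sided. If one-sided testing was intended, say so for every row it applies to.
- **Table 3 note on double difference.** Replace the assurance of more power with double-difference power under a stated between-round correlation of upazila effects, shown over a range. Note that below about 0.6 it falls short of the endline-only contrast (43 v 64 percent, two-sided normal).

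The cost is a few text and table edits and one short calculation, with no new data. The drawback is that the stated figures become less favourable.

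### The stated sensitivity for complementary feeding is not delivered for minimum acceptable diet: the 25 percent statement cannot cover it, and Table 3's 10-point target has about 64% power, not 80%

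*Combined protocol and SAP*

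**What the plan says.** Under Sample size and power calculations, the plan introduces "The estimated sample sizes for each treatment arm, calculated prior to the baseline survey", and these include "500 children 6-23.9 months old for complementary feeding-related practices". The planning conditions are a design "in a total of 20 clusters with an inter-cluster correlation (ICC) of 0.005, a significance level of 0.05, and power of 80 percent". With that sample the study is said to be "sufficient to detect an increase in several complementary feeding practices by at least 25 percent". No practice is named and no baseline is given.

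Percent is relative in this paragraph, because the exclusive breastfeeding target is described as "an increase in EBF rates by approximately 49 percent (from 43 percent to 64 percent".

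The section then points to Table 3 for the detailed calculations. Table 3 has one complementary feeding row, minimum acceptable diet (MAD). Its baseline, detectable difference, baseline ICC and minimum sample size read "14.8 | 10 | 0.04 | 323". A note to the table says the detectable differences are endline-only comparisons between arms and that the double difference will have more power. Under Evaluation Design, sub-districts are randomised "to either the *intensive* (10 sub-districts) or *non-intensive* (10 sub-districts) intervention".

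**The concern.** The section gives two different sensitivities for complementary feeding: a 25% relative rise in the text and 10 points for MAD in Table 3. From 14.8%, 10 points is a 68% relative rise (10/14.8), while 25% would be only 3.7 points. The baseline ICC for MAD, 0.04, is eight times the planning value, and the text does not reconcile the two.

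MAD is a listed impact indicator in Table 6, and complementary feeding has its own planned Bangladesh manuscript. If the design is less sensitive than stated, a null MAD result could be read as evidence against a gain that the study would often have missed.

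**Working it through.** **Inputs.** From Sample size and power calculations: 500 children per arm, 20 clusters, ICC 0.005, alpha 0.05, power 80%. From Evaluation Design: 10 upazilas per arm, so m = 50 children per upazila. From Table 3: MAD baseline 14.8%, detectable difference 10, ICC 0.04, minimum 323.

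**Assumptions.** The test is two-sided; the 10 is in percentage points; 323 is per arm; endline has 500 per arm.

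**Formulas.** Design effect DE = 1 + (m − 1) × ICC. Effective size n = N/DE. SE = √{[p1(1 − p1) + p2(1 − p2)]/n}. Power = Φ[(p2 − p1)/SE − 1.96]. For 80% power the difference must equal (1.96 + 0.842) × SE = 2.802 × SE, and 2.802² = 7.849.

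- ICC 0.005: DE = 1 + 49 × 0.005 = 1.245, n = 500/1.245 = 401.6.
- ICC 0.04: DE = 1 + 49 × 0.04 = 2.96, n = 500/2.96 = 168.9.

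**1. The 25 percent statement.** It cannot be reproduced, because it has no baseline. The baseline p that it needs can be found by setting 7.849 × [p(1 − p) + 1.25p(1 − 1.25p)]/(0.25p)² equal to n. This gives p = 2.25/(0.0625n/7.849 + 2.5625).

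- ICC 0.005: 2.25/(3.198 + 2.5625) = 0.391.
- ICC 0.04: 2.25/(1.345 + 2.5625) = 0.576. This applies MAD's ICC to other practices, so it is only illustrative.

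**2. A 25% rise in MAD (14.8% to 18.5%).** The variance sum is 0.148 × 0.852 + 0.185 × 0.815 = 0.1261 + 0.1508 = 0.2769.

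- ICC 0.005: SE = √(0.2769/401.6) = 0.0263; 0.037/0.0263 = 1.41; Φ(1.41 − 1.96) = 29%.
- ICC 0.04: SE = √(0.2769/168.9) = 0.0405; 0.037/0.0405 = 0.914; Φ(0.914 − 1.96) = 15%.
- With t on 18 df these become 27% and 14%. With no clustering at all, power is 35%.

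**3. Table 3's own MAD target (14.8% to 24.8%, ICC 0.04).** The variance sum is 0.1261 + 0.248 × 0.752 = 0.3126.

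- 500 per arm: SE = √(0.3126/168.9) = 0.0430; 0.10/0.0430 = 2.325; Φ(0.365) = 64% (59% with t on 18 df).
- 323 per arm: m = 32.3, DE = 1 + 31.3 × 0.04 = 2.252, n = 143.4; SE = 0.0467; 0.10/0.0467 = 2.142; Φ(0.182) = 57%.

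Before clustering, 80% power for 10 points needs 7.849 × 0.3126/0.01 = 245 per arm (249 with pooled variance). With 10 upazilas at ICC 0.04, the effective size can never exceed 10/0.04 = 250 per arm, however many children are measured. The requirement lies almost at that ceiling, so the clustered sample size runs well above 10,000 per arm. The 323 is not reproduced for this rise with 10 clusters per arm.

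**4. What 500 per arm detects for MAD, endline-only.** Solving difference = 2.802 × SE:

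- ICC 0.005: 7.7 points (52% relative).
- ICC 0.04: 12.3 points. Check: p2 = 0.271 gives SE = √(0.3235/168.9) = 0.0438, and 2.802 × 0.0438 = 0.123. With t on 18 df it is 13.0 points.

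**5. Double difference, ICC 0.04.** Let r be the correlation of upazila effects between surveys, which the documents do not give. The variance is [3 × 0.1261 + p2(1 − p2)] × [0.96/500 + 0.04(1 − r)/10].

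- r = 0: the second factor is 0.00592 and the detectable difference is 16.6 points.
- r = 1: the second factor is 0.00192 and the detectable difference is 9.2 points.
- To reach 10 points, the variance must be (0.10/2.802)² = 0.001274. The first factor is 0.378 + 0.1865 = 0.565, so the second must be 0.00226. Hence 1 − r = 0.00034/0.004, and r is about 0.92.
- Across both ICCs and r from 0 to 1, power for a 25% rise in MAD is 10-21%.

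**The case against.** A reader might infer that the plan promises 80% power for a 25% rise in MAD and that the promise is false. The documents do not support that reading. The sentence refers to several practices, not all, and does not name MAD. It was calculated before the baseline survey, so neither the 14.8% nor the ICC of 0.04 was available. Table 3 gives MAD its own, much larger target. Table 6 lists four other complementary feeding indicators without baselines, and the 25 percent statement may be right for some of them. It is uncheckable and inapplicable to MAD, which is different from being shown wrong. The 58% threshold at ICC 0.04 should not be carried to other practices either, since ICCs in Table 3 run from 0.00 to 0.12.

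Two further points have force. The planned estimate is a double difference, so an endline-only figure is not the final word. The baseline and endline sample size column of Table 3 is also empty in the text available, so 500 per arm at endline is the proposed size and not a confirmed one.

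Neither removes the problem with the MAD row. Table 3 labels its differences endline-only, so 10 points has to be judged on that basis, at the ICC in the same row. The double difference reaches 10 points only if upazila effects are very highly correlated between surveys.

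**Conclusion.** The point holds in a limited form. The 25 percent statement does not extend to MAD: such a rise has 29% power at the planning ICC and 15% at the baseline ICC. The firmer error is in Table 3. At its own ICC of 0.04 and with 10 upazilas per arm, the 10-point MAD difference has about 64% power with 500 children per arm and about 57% with 323. The endline-only detectable difference is about 12-13 points, from 14.8% to about 27-28%.

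These figures rest on a two-sided 5% test, equal upazila sizes, 500 per arm at endline, 323 read as per arm, and 10 read as percentage points. The table's assurance that the double difference adds power is conditional: the figure runs from roughly 17 down to 9 points as the assumed between-survey correlation goes from 0 to 1.

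**What to change.** - In Table 3, restate the MAD detectable difference as about 12-13 points (14.8% to about 27-28%) for an endline-only comparison with 500 per arm, 10 upazilas per arm, ICC 0.04, two-sided 5% and 80% power. Remove or correct the minimum of 323.
- Reword the note on the double difference to say that its gain depends on the correlation of upazila effects between surveys. For MAD, give the range of roughly 17 to 9 points, or a value based on a stated correlation.
- In Sample size and power calculations, name the practices that the 25 percent sentence covers, with the baseline and ICC of each. Limit it to those that reach 80% power, and say that it does not cover MAD.

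The cost is restating figures. No extra children and no design change are needed; the only downside is a less favourable stated sensitivity.
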